| Objective(s): | 
The study aims to validate the effectiveness and the safety of the new Glucosafe 2 bedside tool. The goal is to improve the management of nutrition support and the glycaemia control for the critically ill patients during their ICU stay.
 
The primary objective is to compare the time spent in a predetermined glycaemia range (5.0 – 8.5 mmol/l) between three groups of patients, all having hyperglycaemia and an expected length of stay in the ICU of <math>\geq 72</math>h:
 
 
1) Intervention group managed with nutrition support and/or insulin infusion pumps adjusted according to advice given by Glucosafe 2;
 
2) Control group receiving Standard Care and
 
3) Historic control group receiving Standard Care.
 
 
The secondary objectives are to bring the energy and protein intake closer to the targets of international recommendations and to reduce the variability of blood glucose.
 
The main safety objective is to avoid hypoglycemia events and reduce hyperglycaemia.
 |
|----------------------|-----------------------------------------------------------------------------------------------------------------------------------------------------------------------------------------------------------------------------------------------------------------------------------------------------------------------------------------------------------------------------------------------------------------------------------------------------------------------------------------------------------------------------------------------------------------------------------------------------------------------------------------------------------------------------------------------------------------------------------------------------------------------------------------------------------------------------------------------------------------------------------------------------------------------------------------------------------------------------------------------------------------------------------------------------------------------------------------------------------|

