Data were collected for four days. The BG target range 5-8 mmol/l. Nutritional targets were individually prescribed by the attending physician and were between 25-30 kcal/d per kg ideal body weight. The mean BG was significantly lower ( $7.0 \pm 1.2$  mmol/l) in Glucosafe patients than in control patients ( $8.0 \pm 1.2$  mmol/l). No adverse events including hypoglycaemia were reported in either group. In the intervention group, 170 (76%) measured BG values were in the 5-8 mmol/l target band, with the lowest BG value at 4.2 mmol/l. In the control group, 171 (51%) measured BG values were in the 5-8 mmol/l target band and the lowest BG was 4.0 mmol/l. The Glucosafe group was closer to isocaloric feeding ( $93.5 \pm 15\%$  of EE) than the control group ( $129.5 \pm 29.4\%$  of EE), but the difference was not significant.

e) In the third pilot study [34], Glucosafe's advice for insulin infusion was administered to 13 hyperglycaemic surgical and medical ICU patients and glycaemia was compared to the pre- and post-intervention days. The BG target range was 5-8.3 mmol/l. Nutrition was provided according to the department guidelines. Fig. 3 shows the cumulated BG measurements over the data collection periods.

[figure not shown]

Figure 3. Distribution of BG during 24h-preintervention (before), 12-14h-intervention (Glucosafe) and 24h-postintervention (after).

During Glucosafe intervention the mean and SD of BG ( $5.8 \pm 0.9$  mmol/l; N=99) was lower than during pre-intervention ( $7.8 \pm 1.8$  mmol/l; N=86) and during post-intervention ( $6.4 \pm 1.4$  mmol/l; N=56). No hypoglycaemic events occurred.

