### **4.3 Secondary Objectives**

The secondary objectives are to assess whether GS2 stabilizes BG and reduces the variability in BG measurements and improves nutritional management by increasing the achievement of the daily energy and protein target by limiting the cumulated energy and protein debt compared to the standard of care.

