### 5.2 Secondary Outcomes

Glycaemic “variability”:

- Mean and SD of BG measurements per day and per patient during the enrolment period
- Maximum of daily BG difference

Achievement of nutritional targets.

- Estimates of energy expenditure, protein requirements, caloric target and protein target are made on a daily basis in the intervention and control groups, as detailed in sect. 8.1.1 and 8.1.2, respectively.
- The caloric target for the day is reached when of 80-100% of the target is achieved.
- The protein target for the day is reached when of 80-100% of the target is achieved.
- Cumulated energy debt, defined as daily energy expenditure minus caloric intake, cumulated over the enrolment period.
- Cumulated protein debt, defined as daily protein requirement minus protein intake, cumulated over the enrolment period.

Prediction of blood glucose (BG)

- Root mean squared prediction error as a measure of the differences between BG predicted by GS2's metabolic model and measured BG. The prediction error will be calculated, as a function of time elapsed since last BG measurement, per patient, per cohort (sect. 9.2.3).

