### 9.2.2 Assessment of secondary outcomes

Glycaemic “variability”:

Mean and SD of BG

- All BG measurement will be reported in the eCRF daily. The mean BG with SD will be calculated from those data.
- Maximum of daily BG difference

Achievement of nutritional targets.

The protein goal is met (e.g., 80-100% of the accumulated target)

- In the control group, the total intake of protein per day is going to be reported in the eCRF. Then, it is going to be compared with the daily target and the percentage will be made. The mean percentage for the duration of the study will then be calculated.
- In the intervention group, the comparison between the daily intake and the daily target is carried out automatically by GS2. The percentage will be reported directly in the eCRF. The mean percentage for the duration of the study will when be calculated.

The caloric goal is met (e.g., 80-100% of the accumulated target)

- In the control group, the total intake of energy per day is going to be report in the eCRF. Then, it is going to be compared with the daily target and the percentage will be made. The mean percentage for the duration of the study will when be calculated.
- In the intervention group, the comparison between the daily intake and the daily target will be made automatically by GS2. The percentage will be directly report in the eCRF. The mean percentage for the duration of the study will then be calculated.

Energy debt at the end of the stay

- In the control group, the total intake of energy per day is going to be reported in the eCRF. The daily energy target will be reported every day as well. Then the total energy debt is calculated as the addition of the daily difference between the energy target and the energy intake.
- In the intervention group, the energy debt will be directly calculated and extracted from GS2.

Protein debt at the end of the stay.

- In the control group, the total intake of protein per day is going to be reported in the eCRF. The daily protein target will be reported every day as well. Then, the total protein debt will be calculated as the addition of the daily difference between the protein target and the protein intake.
- In the intervention group, the protein debt will be directly calculated and extracted from GS2.

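### Cumulated energy and protein debt is a signed sum, so net overfeeding counts as low debt; it suits the deficit objective in 4.3 but cannot by itself show that intake came closer to target

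*Protocol*

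**What the plan says.** **Definitions.** Section 5.2 gives "Cumulated energy debt, defined as daily energy expenditure minus caloric intake, cumulated over the enrolment period" and "Cumulated protein debt, defined as daily protein requirement minus protein intake, cumulated over the enrolment period". Neither definition sets a floor, takes an absolute value or says how a negative result is read.

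**Assessment.** For the control group, section 9.2.2 again uses a signed sum, but against a different reference: "the total energy debt is calculated as the addition of the daily difference between the energy target and the energy intake". For the other arm it says "In the intervention group, the energy debt will be directly calculated and extracted from GS2", without giving the formula.

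**Aims.** There are two.
- The synopsis states: "The secondary objectives are to bring the energy and protein intake closer to the targets of international recommendations". Section 3.5 makes the same kind of statement about nutritional guidelines. This aim is two-sided.
- Section 4.3 wants nutritional management improved "by limiting the cumulated energy and protein debt compared to the standard of care", and section 3.1 also names falling debts as a goal. This aim is one-sided.

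**Other text that bears on overfeeding.** In section 5.2 a day's caloric or protein target counts as reached only between 80% and 100%. Section 3.7 names overfeeding as one of four risk events, and section 10.3.1 lists over-nutrition among the anticipated adverse device effects. Section 11.4.3 compares continuous secondary outcomes by t test or Mann-Whitney test, alongside adjusted regression.

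**The concern.** When less debt is better and the sum keeps its sign, zero is not the best possible score. Net feeding above requirement gives a negative debt, which a t test or rank test treats as lower, hence better, than zero. Averaging over an arm also lets one patient's surplus offset another's deficit, so an arm mean near zero need not mean that patients were fed near requirement.

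This does not matter while every patient runs a deficit, because signed debt and deficit are then the same number. It matters if a material share of patients in either arm end in surplus. A secondary result could then credit the arm that overfed, although the synopsis and 3.5 aim at closeness and the safety sections treat overfeeding as harm.

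**Working it through.** **Planning figures.** The protocol gives none for debt. Its 71 per group is for time-in-target (difference 10 points, SD 21, 80% power, two-sided 5%). It reproduces: 70 by the normal approximation, and 70.2 rounded up to 71 for the t test. It plays no part in what follows.

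**Inputs.** The second study in section 3.3.3 had 6 patients per arm and collected data for four days. Intake was 93.5 ± 15% of EE with Glucosafe and 129.5 ± 29.4% with control. The protocol's own reading is "The Glucosafe group was closer to isocaloric feeding", repeated in 3.3.4. The worked example in 8.1.1 has an EE of 2160 kcal/d, used here only for scale.

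**Step 1: signed debt as in 5.2** (100 minus intake, % of EE per day).
- Glucosafe: 100 - 93.5 = +6.5
- Control: 100 - 129.5 = -29.5
- Difference: 6.5 - (-29.5) = 36 points, in favour of control

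In kcal over four days: 0.065 × 2160 × 4 = +562, against -0.295 × 2160 × 4 = -2549.

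**Step 2: distance of each arm mean from EE.** This is 6.5 points against 29.5 points, in favour of Glucosafe. The ranking reverses, and no distributional assumption is needed.

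**Step 3: patient-level quantities.** Assume that ± is the between-patient SD and that intakes are normal. With m = 100 - mean and s = SD:
- mean deficit = m·Φ(m/s) + s·φ(m/s)
- mean surplus = mean deficit - m
- mean absolute deviation = mean deficit + mean surplus

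Glucosafe, m/s = 0.433: deficit = 6.5 × 0.668 + 15 × 0.363 = 9.8.
Control, m/s = -1.003: deficit = -29.5 × 0.158 + 29.4 × 0.241 = 2.4.

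| % of EE per day | Glucosafe | Control | Lower in |
|---|---|---|---|
| Signed debt | +6.5 | -29.5 | Control |
| Deficit, floored at zero | 9.8 | 2.4 | Control |
| Surplus | 3.3 | 31.9 | Glucosafe |
| Absolute deviation | 13.1 | 34.4 | Glucosafe |

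Flooring at zero alone therefore does not measure closeness. The surplus must be counted too.

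**Step 4: cancellation between patients.** Take two patients with equal EE, one fed 50% and the other 150%. Their signed debts are +50 and -50, with mean 0. That is the same mean as for two patients both fed 100%, yet the mean absolute deviation is 50% rather than 0.

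**Step 5: reference quantity.** Under 8.1.1 the GS2 caloric target is EE times an acuteness factor that starts at 20% and rises by 10 points per nurse shift to 100%. Assume three shifts a day, default settings and counting from admission. A patient fed exactly to target then falls short of EE by (80 + 70 + … + 10)/100 = 3.6 shift-equivalents, or 3.6/3 = 1.2 days of EE (2592 kcal at 2160 kcal/d). Debt against target is zero. Debt counted from a later enrolment is smaller. The choice between 5.2 and 9.2.2 therefore changes the result.

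**The case against.** The strongest reply is that debt is meant to measure the deficit side and does so. Section 4.3 asks for limited debt, the synopsis ties caloric debt to weakness after the ICU, and 3.1 describes underfeeding as the usual problem. Closeness is served by another outcome in the same list, the 80-100% attainment, which fails a day above 100% and has its own mixed-effects logistic model in 11.4.3. Over-nutrition is also foreseen among the adverse device effects. This stands: debt matches the wording of 4.3, and overfeeding is not unguarded. But attainment is a yes/no measure that scores 105% and 180% of target alike, so it neither measures distance nor corrects a debt comparison that points the other way.

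A second reply is that the protocol never says negative beats zero, that limiting a debt is not the same as seeking a surplus, and that a negative group mean would be visible. The first two parts are fair. But the formula and the type of test are already in the protocol, and both tests order negative values below zero. Visibility of a negative mean does not help when surpluses and deficits cancel.

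Third, within-patient netting is intended, since 3.1 says GS2 can to a degree make up earlier deficits. This stands, and the fix keeps it.

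A reader might also infer from the predecessor study that this trial's debt result will favour the wrong arm. The documents do not support that. That study had 6 patients per arm, was stopped early, and its intake difference was not significant. In this trial both arms build feeding up gradually (8.1.1, 8.1.2), which makes positive debt likely early on.

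**Conclusion.** The point holds for the debt outcomes only. As defined in 5.2, and in 9.2.2 for the control group, debt credits net overfeeding and lets patients cancel in an arm mean. It can inform the deficit objective of 4.3 but cannot alone support the closeness aim of the synopsis and 3.5. On the protocol's own predecessor figures the formula gives a 36-point advantage to the arm that the protocol regards as further from isocaloric feeding. That shows the mechanism; its size in this trial depends on how many patients end in surplus, which the protocol does not let one estimate.

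It would go too far to say that the nutrition outcomes as a whole reward overfeeding, or that debt contradicts its own objective: the 80-100% outcome has a ceiling, and 4.3 does ask for less debt. For the intervention arm, the signed reading rests on 5.2 alone, because 9.2.2 does not show the GS2 formula. The patient-level figures in step 3 also rest on normality and on reading ± as SD. The outcomes are secondary, and the primary outcome and sample size are unaffected.

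**What to change.** Amend 5.2 and 9.2.2, for energy and for protein alike.

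1. Keep the running net balance within each patient, B = Σ(requirement - intake) over enrolment, so that repaying an earlier deficit is not penalised.
2. At the end of enrolment report three quantities per patient: net deficit, max(0, B), for the 4.3 objective; net surplus, max(0, -B), beside it; and absolute deviation from cumulated requirement, |B|, as the between-arm comparison for the closeness aim.
3. State that a negative signed debt is not read as better than zero.
4. Apply the same formula in both arms. Confirm what the GS2 extract computes, or recompute debt from daily requirement and intake.
5. Reconcile the reference quantity: 5.2 uses energy expenditure and protein requirement, while 9.2.2 uses the daily targets in the control group.

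The cost is a short redefinition and a few extra secondary rows. Daily intakes and targets are already recorded, and 5.2 provides for daily estimates of expenditure and protein requirement in both randomised arms.

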| Design:                         | 
Randomized controlled study with an intervention group, a control group; a historical control group will also be studied:
 
 
- Intervention group: Glucosafe 2 is used until the patient is discharged from the ICU or for a maximal follow-up of 15 days or when he/she starts eating (voluntary feeding). Number of patients: 71
 
- Control group: Standard care according to local ICU protocols (Geneva-HUG). The maximal follow-up is of 15 days or when he/she starts eating (voluntary feeding). Number of patients: 71.
 
- Historical control group: retrospective data from a random sample of 71 patients exposed to the standard care regarding nutrition support and glycaemic control and recruited before the beginning of the pilot study in order to minimize the “cross-over” effects and to confirm the predictive accuracy of Glucosafe2. Historical controls’ data will be retrospectively harvested from the patients’ computerized record. They will be recruited within 2 years before the trial start.
 
 |
| Inclusion / exclusion criteria: | 
Inclusion criteria:
 
All patients <math>\geq 18</math> years old admitted in adult ICU- Geneva with
 
 
• An expected length of stay <math>\geq 72</math>h
 
• At least 1 blood glucose (BG) measurement <math>\geq 10</math> mmol/l or 2 BG measurement <math>\geq 8.5</math> mmol/l
 
• Informed Consent signed by the subject/ legal representative, except for patients in the historical control group
 
 
Exclusion criteria:
 
 
• Lack of legal consent or consent withdrawn, except for patients in the historical control group
 
• Pregnant or breast feeding
 
• Diabetic ketoacidosis or hyperosmolar state
 
• Oral feeding
 
• Fulminant hepatic failure
 
• Medically contraindicated to receive rapidly acting insulin by intravenous (iv) infusion or iv injection
 
                                                                                                                                             |

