| Measurements and procedures: | 
Screening will be done every day (Monday to Friday). Eligible patients will be randomly allocated to either intervention or control group. Before inclusion, all patients will be treated according to the ICU- Geneva Protocols.
 
Collected data:
 
Baseline at study inclusion day
 
 
- Body mass, height and body mass index (BMI)
 
- Age, gender
 
- Date and time of admission in the ICU
 
- Primary diagnostic
 
- Known chronic illness (diabetes, acute kidney injury (AKI), pancreatitis, tumor, etc.).
 
- Medication influencing glycaemia (oral antidiabetics' insulin, steroids, prednisone, etc.).
 
- Renal and hepatic status
 
- Glycaemia and lactate
 
- Vitals
 
- Severity score (APACHE II, SAPS II) at ICU admission
 
 
Daily data from inclusion day (maximum follow up of 15 days)
 
When possible – Following routines measurement.
 
 
- Glucose measurements
 
- Other laboratory: lactate, CRP, sodium (Na), potassium (K), glycohemoglobin (HbA1C), urea, creatinine, glomerular filtration rate (GFR), protein, albumin, ASAT, ALAT, phosphatase alkaline, γ-glutamyltranspeptidase (GGT), bilirubin
 
- Any events (intubation, extubation, length of surgery, infusions, cardiac events, infections, requirement for red blood cell (RBC) transfusion, hemodynamic rate (HR), organ failure)
 
- Vitals (blood pressure, temperature, heart rate etc.)
 
- Antibiotics usage
 
- Vasopressor
 
- Steroids
 
- Propofol® for sedation
 
- Glucose perfusion
 
- Insulin therapy including boluses.
 
- Body weight, BMI, Ideal body weight (if needed), presence of oedema.
 
- Energy expenditure (IC or predictive formula)
 
- Energy and protein targets over the day
 
- Prescription and administration (ml of product, kcal and grams of protein).
 
- Daily water balance
 
- Diuresis
 
- Diarrhoea, constipation
 
- Nausea, Vomiting, gastric residual
 
- Physical therapy
 
- Medical Research Council Scale (MRC Scale)
 
 
Upon ICU leave
 
 
- Duration of ICU stay
 
- MRC Scale at ICU discharge
 
- Alive status at ICU discharge
 
- Duration of hospitalization
 
- Alive status at hospital discharge
 
- BMI at hospital discharge
 
 |

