### 5.3 Other Outcomes of Interest

Workload:

- Frequency of daily and cumulated BG measurements per patient and in the cohort during the patient's enrolment period (duration of the ICU stay with a max of 15 days).
- Frequency of daily and cumulated adjustments of insulin and nutrition pump settings during the patient's enrolment period.

Compliance (only in intervention arm)

- Number of episodes per patient and in the cohort where a BG measurement is not followed up within 30 minutes by an accepted GS2 advice (during the enrolment period)
- Number of episodes per patient and in the cohort where GS2 advice was accepted by the nurse but pumps were not set according to the advice within 30 min by the nurse (nurse did not notice, was too busy, forgot, or misinterpreted advice = true errors)
- Number of advices given by GS2 which were accepted, accepted with modification or rejected

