## Setting the nutritional targets

The screenshot shows the 'Nutrition target' page in the GS2 system. At the top, there's a navigation bar with 'Glucose', 'Safe', 'Settings', 'Patients', 'Advice', 'Nutrition target' (selected), and 'System log'. Below this, a patient header shows 'Patient: [name] M 45 yrs, 2 d. ICU, non-diabetic, unknown', 'User: [name] (administrator)', and '00:04:24'. A status bar indicates 'Length of ICU stay: 45 hours', 'Number of nurse shifts: 6', and 'Acuteness factor: 70 %' with an 'apply' button. The main content area is divided into two columns: 'Caloric Target' (highlighted in pink) and 'Protein Target' (highlighted in blue). The 'Caloric Target' column has three sub-sections: 'Indirect Calorimetry' (Last measured: 29/01 15:40, Value (kcal): 2160, 'apply' button), 'Free estimate' (empty input, 'apply' button), and '25 kcal/kg/d' (Weight estimate: 95 kg, BMI: 24.2 kg/m², Ideal Weight: 88.2 kg, 2280 kcal/d, 'apply' button). Below these, 'Current Energy Expenditure (EE)' is 2160 kcal/d. The 'Protein Target' column shows 'Daily requirement: 1.3 g/kg/d', 'Actual weight: 95 kg', and 'Ideal weight: 88.2 kg'. Below this, 'Proteins required' is 124 g/d. The bottom section, 'During recovery phase (post-acute phase)', shows 'Total caloric intake since ICU admission: 71 % of cumulated energy expenditure', 'Recovery factor: --', and 'Final Caloric Target (post-acute phase): --'. The 'Protein Target' column also shows 'On hemofiltration (IHF or CHF):', 'Is HF (CHF or IHF) currently in use? yes', 'Compensation for amino acid (AA) losses: 130 %', and 'Final Protein Target: 112 g/d'.

Figure 6. The page used in GS2 to set the nutritional (caloric and protein) targets.

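### Energy and protein debt are not computed the same way in the two randomised arms, and are defined as unscaled totals over follow-up of varying length

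*Protocol*

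**What the plan says.** Limiting cumulated energy and protein debt is part of the secondary objective (Protocol 4.3). Section 5.2 defines the two outcomes as "Cumulated energy debt, defined as daily energy expenditure minus caloric intake, cumulated over the enrolment period" and "Cumulated protein debt, defined as daily protein requirement minus protein intake, cumulated over the enrolment period", with no distinction between arms.

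Section 9.2.2 describes the calculation. For controls, daily intake and daily target are entered in the eCRF, and the debt is the sum of the daily differences between target and intake. For the other arm, "In the intervention group, the energy debt will be directly calculated and extracted from GS2"; protein debt is handled the same way. Neither the formula nor the start of the exported figure is given.

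On timing, the Synopsis lists intake under "Daily data from inclusion day (maximum follow up of 15 days", and the investigation schedule marks energy and protein intake only in the intervention period. GS2's example nutrition page (section 8.1.1, Figure 6) reads "Total caloric intake since ICU admission: 71 % of cumulated energy expenditure". Section 5.3 explains the enrolment period as "duration of the ICU stay with a max of 15 days".

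On the end of observation, the Synopsis says "Glucosafe 2 is used until the patient is discharged from the ICU or for a maximal follow-up of 15 days" or until the patient starts eating. Section 7.4 adds death, withdrawal of life support and withdrawal of consent.

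**The concern.** A randomised comparison of an outcome is fair only if the outcome is measured alike in both arms. Here the written calculation differs in source, possibly in reference quantity and possibly in start. Any of these can create or hide a difference in debt that has nothing to do with how patients were fed.

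Separately, each debt is a sum that stops growing when the patient dies, eats, leaves the ICU or reaches day 15. All else equal, an early stop gives a small debt. The protocol divides by observed time for its primary outcome (section 5.1) but not here.

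**Working it through.** **The plan's own figures.** The only sample-size figure is 71 per group, for time in target: 2 × (1.96 + 0.84)² × 21² / 10² ≈ 69.1, or 70 per group by the normal formula. The t test gives 79.9% power at 70 and 80.4% at 71, so 71 reproduces. It was not chosen for the debt outcomes. The Figure 6 caloric target also reproduces: 2,160 × 0.70 = 1,512 kcal/d.

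**1. Reference quantity.** Section 5.2 uses expenditure or requirement; section 9.2.2 uses target for controls. Within GS2 the two are apart whenever the acuteness factor is below 100%:
- Energy: 2,160 − 1,512 = 648 kcal/d.
- Protein: 124 − 86 = 38 g/d, or 124 − 112 = 12 g/d after the hemofiltration adjustment shown on that screen.

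By default the factor starts at 20% and rises by 10 points per nurse shift, so this gap closes after (100 − 20)/10 = 8 increments. An export counted against target would make GS2 debt look smaller than one counted against expenditure.

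**2. Start.** If the export counts from admission, as the example screen does, and the patient is included at about 45 h (assumed), the debt already owed is 2,160 × 45/24 × (1 − 0.71) = 4,050 × 0.29 ≈ 1,175 kcal. This acts against GS2. The reference effect could act for it, so the net direction cannot be read from the protocol.

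**3. Effect of such an offset.** Simulation, 71 per arm, 4,000 trials. Assumed, not in the protocol: mean deficit 400 kcal/d, between-patient SD 300 to 400, gamma follow-up with mean about 8 days cut to 2–15.
- Equal feeding, 1,175 kcal added to GS2 only: significant in 46–63% of trials.
- True benefit of 200 kcal/d: power on the total falls from 71–89% without the offset to 9–12% with it.

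**4. Effect of unscaled totals.** At 2,160 kcal/d and 80% intake, identical feeding gives 432 × 3 = 1,296 kcal at 3 days, 3,024 at 7 and 6,480 at 15. In the same simulation:
- Equal feeding and equal follow-up: about 5% false positives, so variable length alone does not bias the randomised comparison.
- Equal feeding, GS2 followed nominally 1 day less: spurious difference about −320 to −345 kcal, significant in 8–11%. With 2 days less: about −685 to −705 kcal, 22–34%.
- Share of the variance of the total: days 17–27%, daily deficit 59–67%.
- Power for 200 kcal/d with equal follow-up: 71–89% on the total, 84–97% per day.

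A second set of assumptions (500 against 350 kcal/d, SD 300, mean follow-up 6–8 days, SD 3–4.5) gives 59–63% on totals and 83–85% per day.

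**5. Is division by days enough?** Section 8.1.2 describes feeding built up to 80–100% of target by the end of day 3, so deficits are likely larger early. Assume identical feeding, a later deficit of 300 kcal/d (SD 300), and extra early deficits of 800/400 or 1,200/800/400 kcal on the first enrolled days. With GS2 observed 1–2 days longer, false positives are 9–68% per day against 8–33% on totals. Simple division is no cure.

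**The case against.** The strongest defence is that section 5.2 sets one window and one formula for everyone, and that the export may be cut to fit them. The instructions for use and the automatic eCRF export template, which could show this, are not at hand. The count from admission is one percentage in the recovery-phase box of an example page; nothing says it is the exported debt. This stands as a limit on the start-time point, which remains an inference. It does not settle the conflict between 5.2 and the control-arm rule in 9.2.2, which is on the page.

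A second defence is that scaling and modelling are commonly left to a SAP, and that daily target attainment and mean percentage of target do not grow with length. That is fair as far as it goes. However, the protocol itself fixes the arm-specific calculation. The percentages also use each arm's own target: 1,512 kcal delivered in the GS2 example is 100% of target but 70% of expenditure.

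A reader might infer that length of follow-up, rather than feeding, drives the debt comparison. The protocol does not support this: nothing in it shows that follow-up will differ by arm, and under the assumed values the daily deficit explains more of the total than days do. A reader might also state as fact that pre-randomisation debt is charged to GS2 only; no section says so. Nor should GS2's default ramp be applied to the 48 h before inclusion (0.55 × 2,160 × 2 = 2,376 kcal), because the Synopsis and section 7.2.1 place all patients under local protocols until then.

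**Conclusion.** The definition in 5.2 and the calculation in 9.2.2 contradict each other, and 9.2.2 writes a measurement difference between the randomised arms into a named secondary objective. That much is documented. The 648 kcal/d gap comes from the protocol's single example and applies only while the acuteness factor is below 100%. The 1,175 kcal head start comes from the same screen and holds only if the export counts from admission.

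The unscaled total is a lesser fault. It costs power, about 60% against 84% under one set of assumptions and 71–89% against 84–97% under another. It biases the randomised comparison only if follow-up or start differs by arm. The comparison with historical patients (section 11.4.1) has no randomisation to equalise follow-up. All power and false-positive figures rest on assumed deficits, SDs and lengths of follow-up.

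**What to change.** In sections 5.2 and 9.2.2:
- Compute debt in both randomised arms from the same administered kcal and protein records, with the 5.2 formula (expenditure or requirement minus intake), counted from randomisation to the end of enrolment.
- Align the explanation of the enrolment period in 5.3, and give historical patients an equivalent start rule.
- Use the GS2 export only as a cross-check.
- Compare daily deficits with the mixed-effects linear model already planned in 11.4.3, with study day as a covariate, preferably categorical because deficits need not fall in a straight line. Do not rely on the total or on simple division by days.
- Report the cumulated total alongside, with days observed and deaths by arm.

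The cost is a few sentences. The Synopsis already lists daily expenditure, targets and administered kcal and protein. Daily protein requirement is promised in 5.2 but not named in that list, so its eCRF field should be confirmed. The downside is that the cumulated total, which the objective names, becomes a supporting figure rather than the one compared.
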